### Randomization

Cluster randomization among locations of the care centers will be used to prevent crossover effects between professionals and parents/relatives. Group homes and activity centers will be randomly assigned to the treatment condition or the care-as-usual condition by an independent party, based on order of entry and a pre-determined order of treatment conditions. Randomization of participants will occur after enrollment but before the baseline assessment. Participants are to be informed of their allocated condition shortly after T0 to reduce any response bias during the baseline assessment.

### Blinding

The research team will remain blind to the assigned condition of participants. Blinding participants to treatment condition will no longer be feasible after T0, when the assignment to conditions is revealed.

### Intervention

The HiSense APP-ID uses questions, statements, and practical examples to inform parents/relatives and professional caregivers about the influence of their sensitivity and responsivity in the context of attachment and communication. The m-learning intervention is divided into short, daily sessions. In addition to the advantage of taking little time, this approach is beneficial for the learning process. The topics are revisited repeatedly over time in different questions, leading to durable embedding in memory [32–34].

The main topics in the intervention are (1) attachment theory in daily practice, (2) socio-emotional functioning in persons with ID, (3) sensitivity and responsiveness to communicative signals, (4) emotion regulation, (5) observation and interpretation of behavior, and (6) basic knowledge about ID and common comorbidities such as autism spectrum disorder and attention deficit hyperactivity disorder. Each topic is addressed in 15 questions, except for attachment theory, which has 45 questions. Phrasing is differentiated for parents/relatives and professional caregivers, corresponding to their relationship to individuals with ID. For example, a question for professional caregivers is, “What does your client need to form a secure attachment relationship?” while for parents/relatives, the question is, “What does your child need to form a secure attachment?”

The intervention was developed in collaboration with healthcare professionals and parents/relatives of persons with mild and moderate ID. An advisory board of healthcare professionals was first consulted to determine the main topics of our first draft. The items were then judged by parents and professional caretakers on three points: (1) clarity of the questions, (2) clarity of the explanation, and (3) perceived relevance of the information. A total of 14 professional caretakers individually judged 12 items at random. Their comments were incorporated into the final revision of the content.

The structure of the intervention follows the first three categories of Bloom’s taxonomy of educational objectives ([35]; see [36] for adaptations): remember (acquisition of knowledge), understand (processing the content at a surface level), and apply (executing, implementing). The first 10 days (questions 1– 40) focus on background knowledge. On days 11–20 (questions 41–80), this knowledge is explicitly linked to practice, and on days 21–30 (questions 81–120), the items contain more elaborate examples and require deeper knowledge of the theory. Higher-level processing and application (the stages analyze, evaluate, and create) must then follow in daily practice.

### Measures

#### Demographics (T0)

At T0, the participants will answer questions on demographic characteristics, such as age, sex, level of education, work experience, and the relationship to the person with ID.

#### Empathy (T0, T1, T2)

The Empathy Quotient (EQ) questionnaire [18] (Dutch translation by De Corte and Uzieblo [37], adapted by Volman [38]), contains 60 items with a 4-point Likert scale. Participants indicate their level of agreement with statements regarding their sensitivity in social contexts. This study will use the abridged version of 40 items [18]. The EQ has high test–retest validity (*r* = .97, *p* < .001) and high internal consistency [39] (α = .92).

The Interpersonal Reactivity Index [40] (IRI) contains 28 items, divided over four subscales (perspective taking, fantasy, empathic concern, and personal distress). Participants indicate on a 5-point Likert scale how well each statement describes them. All subscales have sufficient internal reliability (.71–.77) and test–retest reliability (.62–.72).

#### Self-efficacy (T0, T1, T2)

The Self-Efficacy in the Nurturing Role scale ([41], translated [42]) is used to measure experienced competence of the participants. Participants answer 16 items about their role and experienced competence as a caregiver. On a 4-point Likert scale, respondents indicate to what extent the statements describe them. The scale has high internal consistency [41].

#### Knowledge (T0, T1, T2)

A short test of 25 multiple choice questions has been developed parallel to the development of the intervention. For each of the six main topics, one question is asked at the level of remembering, two questions assess understanding, and one question tests the ability to apply knowledge in a practical context. One additional question has been added to each test that requires applied knowledge of attachment theory in daily practice. Questions are similar to items in the intervention and differ at each measurement.

#### Social validity (T0, T1)

Participants will complete the Social Validity Scale [43] in the version as described by Janssen et al. [44] and Jonker et al. [45]. The questionnaire contains 32 items with a 5-point Likert scale on their expectations for the HiSense APP-ID (T0) or their experiences (T1) in terms of its practical use, their motivation for pursuing the intervention, and perceived effects on the quality of their care for their family member or client.

### Procedure

Participants will be recruited by the participating care centers. First, the centers will acquire groups of professional caregivers who work together in group homes or activity centers for persons with mild or moderate ID. Next, parents/relatives of clients will be approached for participation. If needed, recruitment for parents/relatives can be extended to other group homes and other care centers. All participants will be asked to give active consent for participation.

The study will contain three time points of data collection (Fig. 2): before the start of the intervention (T0), at the end of the intervention (40 days after T0), and 30 days after T1. For professional caregivers, researchers will make an appointment at the residence and provide a laptop to complete the questionnaires. Family members can come to the care center or complete the questionnaires online at home. Each measurement will take 45 min.

After T0, participants in the intervention condition will be asked to use the HiSense APP-ID for a total of 30 days. Each day, participants will complete four multiple-choice questions, which takes a maximum of 5 min per day. They will receive feedback on their original answer (correct or wrong) and an additional explanation for the correct answer. Participants do not have to log in on weekends, but after 2 days of inactivity, they are reminded of their participation by an automatic email. If a participant has not been active for 5 days, that person is excluded from further participation. There are 120 questions in total, which should be completed within 40 days. At the end of day 10 and day 20, participants can revisit the questions that were answered incorrectly. Participants in the “waiting list condition” receive care as usual.

At 40 days after T0, the knowledge tests and questionnaires are completed again by participants in both conditions (T1, see Fig. 1). After a retention period of 30 days, the questionnaires are completed for the last time (T2). Participants in the care-as-usual condition are then encouraged to use the app.

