### Recruitment

The study will include two samples. The participants will be 100 professional caregivers and 100 parents/relatives of adults with mild or moderate ID (intelligence quotient (IQ) 35–70). This also included persons with ID and additional psychiatric diagnoses such as autism spectrum disorders, or additional physical disabilities such as a visual impairment. The group of professional caregivers will be recruited within three Dutch centers providing care for persons with ID living in group homes. Each care center has multiple group homes and activity centers in The Netherlands. The group of parents/relatives of adults with mild or moderate ID will be recruited from these and other centers throughout The Netherlands. Close relatives, such as a brother, sister, uncle, or aunt, can participate if the parents of a client are no longer the primary caregivers.

Participants in both samples will be recruited and enrolled by the participating care centers, which combined are connected to 3107 professional caregivers and 4830 parents/relatives. Participants will be invited to participate when they care for one or more persons with mild or moderate ID.

Candidates will be excluded from participation when they primarily care for persons with severe intellectual disability (IQ below 35) or when their use of HiSense APP-ID will be interrupted for more than five consecutive days. For parents/relatives, only one family member per client is included.

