### Data analysis

All statistical analyses will be conducted using SPSS version 23 [46]. Both groups of participants (parents/relatives and professionals) will be treated as separate groups in the analyses because we expect that matching will not be possible. Partial intention-to-treat analyses will be performed: participants will be excluded from the analysis if fewer than two data points are available. All other participants will be analyzed according to their assigned condition.

For social validity, empathy, and self-efficacy, average item scores will be reported for each questionnaire. For the knowledge test, the total number of correct answers is to be used. Reliability statistics (Cronbach’s alpha) will be reported for the knowledge test at T0, T1, and T2.

Descriptive statistics will summarize the characteristics of the participants. Demographic variables are recorded as categorical variables, so chi-square analyses will be used to determine whether there are statistical differences between participant groups in the experimental and control condition at T0.

Increases in knowledge, empathy, and self-efficacy will be assessed using linear mixed effects modeling. Condition will be entered as a fixed effect and intercepts for participant and care center as random effects. Demographic variables will be included as a covariate in the analysis if significant between-group differences are found at T0.

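### Excluding app users after 5 inactive days, combined with the two-data-point rule, allows an engagement-based exclusion after randomisation whose trigger exists only in the intervention arm

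*Protocol article*

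**What the plan says.** All references are to the protocol article.

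- **Randomization:** "Randomization of participants will occur after enrollment but before the baseline assessment". Participants learn their allocation shortly after T0.
- **Procedure, app use:** "After T0, participants in the intervention condition will be asked to use the HiSense APP-ID for a total of 30 days". The same paragraph asks for all 120 questions to be finished within 40 days, requires no login at weekends, sends a reminder after 2 inactive days, and then states: "If a participant has not been active for 5 days, that person is excluded from further participation".
- **Procedure, assessments:** "At 40 days after T0, the knowledge tests and questionnaires are completed again by participants in both conditions". T2 follows 30 days later. Of the control arm after T2 it says: "Participants in the care-as-usual condition are then encouraged to use the app".
- **Data analysis:** "Partial intention-to-treat analyses will be performed", which is spelled out as "participants will be excluded from the analysis if fewer than two data points are available". Everyone else is analysed in the assigned arm.
- **Recruitment:** candidates are not enrolled "when their use of HiSense APP-ID will be interrupted for more than five consecutive days".

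**The concern.** Randomisation protects the comparison only if who is analysed does not depend on what happens after allocation. Here the protocol itself appears to end follow-up for people who disengage from the app, and the analysis rule then deletes them. Control participants of equal motivation face no such test during the trial.

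At stake is what the trial estimates. The sponsor wants to know whether offering the app improves knowledge, empathy and self-efficacy. An app arm reduced to those who kept logging in answers a narrower question and is no longer fully comparable with the control arm. The issue is not remote: the Discussion itself doubts whether participants working on their own will keep going for the full course.

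**Working it through.** **Step 1. Do the rules combine as feared?**

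1. Randomisation precedes T0 and app use follows T0, so any removal for inactivity comes after randomisation.
2. The course must be completed within 40 days and T1 is 40 days after T0, so such a removal normally falls before T1.
3. A person who leaves the study at that point has T0 only: 1 data point. Since 1 < 2, the person is not analysed.
4. Controls have no app to be inactive on until after T2, so the trigger cannot reach them.

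**Step 2. The plan's own loss figure.** Sample size gives about 90 participants plus 10% for attrition. 90 / (1 − 0.10) = 100, and 90 × 1.10 = 99, so the stated 100 per sample is reproduced either way. The Abstract puts half of each sample in the intervention, about 50. If the whole allowance (10 of 100) fell in the app arm, that would be 10 / 50 = 20% of it, leaving about 40 against 50. This shows what the allowance could hide; it is not a forecast.

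**Step 3. Size of the bias.** Let *d* be the share of the app arm removed, and *g* the amount, in SD and beyond what T0 explains, by which those removed would have scored below those kept. The full-arm mean is (1 − *d*) × mean kept + *d* × mean removed, so

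mean kept − full-arm mean = *d* × *g*.

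If controls also lose a share *d*c with gap *g*c under the two-data-point rule, the net bias is *d* × *g* − *d*c × *g*c. The figures below isolate the inactivity rule, so the second term is set to 0.

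The document gives neither *d* nor *g*. Both are assumptions.

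| *d* | *g* = 0.3 SD | *g* = 0.5 SD | *g* = 0.8 SD |
|---|---|---|---|
| 10% | 0.03 | 0.05 | 0.08 |
| 20% | 0.06 | 0.10 | 0.16 |
| 30% | 0.09 | 0.15 | 0.24 |

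Against the 0.5 SD target, the ends of the range are 0.03 / 0.5 = 6% and 0.24 / 0.5 = 48%. With *g* = 0 there is no bias. With *g* negative it runs against the app: at *d* = 20% and *g* = −0.25 it is −0.05 SD. I do not convert these figures into type I error, because that would also depend on the cluster allocation and the repeated-measures model.

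**Step 4. Would dropping the two-data-point rule be enough?** No. A T0-only record carries no post-intervention outcome. In effect the mixed model would treat that person as developing like retained users in the same arm with similar T0 scores, which is doubtful for someone who stopped seeing the material.

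**The case against.** The strongest reply is that the inactivity sentence sits among the instructions for daily app use and may end app use only. The protocol never says that T1 and T2 are withheld, and the next paragraph has participants in both arms completing T1. On that reading the two-data-point rule keeps these people and the bias disappears. This cannot be ruled out. Leaving the study is still the more natural reading: Recruitment uses almost the same participation wording for exclusion from the study, and nothing says that removed users are still assessed. If an app-only rule is meant, the text has to say so.

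Several stronger readings are tempting but not supported:

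- *The control arm is unselected.* It is not. Controls who miss both T1 and T2 also fall under the two-data-point rule. Only the inactivity trigger is specific to one arm.
- *Every outcome is certainly biased upward.* The direction depends on *g*, which the document does not give. Upward bias is most plausible for knowledge, because the test items resemble the app items and inactive users saw fewer of them. It is less evident for general empathy questionnaires.
- *Social validity at T1 is collected only from continuing users.* The Social validity section does not say this. It would follow only from the study-exit reading.
- *The two five-day statements contradict each other.* One concerns an interruption foreseen at entry, the other observed inactivity during use. They act at different stages and need not share a threshold. How they relate, and whether weekend days count, is unclear rather than contradictory.

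Nor is it a fault that the attrition allowance is not split by arm or cause; a protocol article need not do that.

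**Conclusion.** The point holds. On the natural reading, two stated rules together remove less engaged app users from the analysis after randomisation, through a trigger that controls cannot meet. It is not a detail that an analysis plan could supply later, because no analysis recovers T1 and T2 data that were never collected.

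The likely direction favours the app, chiefly on knowledge and, if those who stopped are not asked, on reported experience at T1. The illustrative range of 0.03–0.24 SD rests wholly on the assumed 10–30% removed and 0.3–0.8 SD gap, with no offsetting selection among controls. The conclusion about the design does not depend on any particular value in that range.

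**What to change.** 1. Separate app use from study participation in the Procedure section. State that every randomised participant is invited to T1 and T2 whatever their app activity. This is the essential step.
2. Replace the two-data-point exclusion with a mixed model in the assigned arm that uses all available measurements. Without step 1 this adds little.
3. Report app completion as an adherence measure, with a completer analysis labelled as supportive.
4. State whether weekend days count towards the 5 days and how that rule relates to the entry criterion in Recruitment, so that the two passages are reconciled.

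The cost is two 45-minute assessments per inactive user. Professional caregivers are already seen by appointment at the residence, and relatives can attend the care center or answer online. The estimated effect may be smaller because low users are included, but it then describes the effect of offering the app. Trial status places the start of data collection after the date of this protocol version, so on that timetable the change could precede any loss of data.

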### Data recording

Privacy of the participants will be guaranteed by the use of personal identification numbers, to be assigned by a contact at the care centers. An email address is used only to send reminders during the intervention and to send a certificate of participation after completion of the intervention. Personal information about potential and enrolled participants will be kept within the organizations. Researchers will not see the names of the participants, and no detailed information will be obtained from the participants.

Questionnaires will be presented to participants in the digital Qualtrics web environment, which is accessed with a personal code. A guideline for using this program has been issued by the university’s ethical committee, which will be followed. Participants log into Qualtrics using only their identification number. To ensure anonymity of the participants, the program will not register the internet protocol (IP) address. No research data will appear on paper, and only the principal researchers will have access to the digital data. The data are stored according to the guidelines of the American Psychological Association until 10 years after publication of the results.

### Data management and monitoring

All data will be collected through computerized assessments, which obviate the need for double data entry. A data monitoring committee has not been established, because of minimal risks for the participants involved. A data management plan has been submitted to and accepted by the funding organization of the study (ZonMw), project number 845004004. The funding organization will conduct yearly site visits to check on the progress of the project.

This study is embedded in the Amsterdam Public Health (APH) research institute. The quality committee of APH has created an electronic quality assurance handbook to unify the conduct and safeguard the quality of research within the institute. In addition, APH randomly audits all projects to assure their quality. This study adheres to the quality handbook and anticipates the possibility of being randomly audited.

### Data analysis

All statistical analyses will be conducted using SPSS version 23 [46]. Both groups of participants (parents/relatives and professionals) will be treated as separate groups in the analyses because we expect that matching will not be possible. Partial intention-to-treat analyses will be performed: participants will be excluded from the analysis if fewer than two data points are available. All other participants will be analyzed according to their assigned condition.

For social validity, empathy, and self-efficacy, average item scores will be reported for each questionnaire. For the knowledge test, the total number of correct answers is to be used. Reliability statistics (Cronbach’s alpha) will be reported for the knowledge test at T0, T1, and T2.

Descriptive statistics will summarize the characteristics of the participants. Demographic variables are recorded as categorical variables, so chi-square analyses will be used to determine whether there are statistical differences between participant groups in the experimental and control condition at T0.

Increases in knowledge, empathy, and self-efficacy will be assessed using linear mixed effects modeling. Condition will be entered as a fixed effect and intercepts for participant and care center as random effects. Demographic variables will be included as a covariate in the analysis if significant between-group differences are found at T0.

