#### Primary hypotheses

The primary hypotheses are:Participation in the intervention will be associated with an increase in theoretical knowledge about sensitive and responsive interaction, for both parents/relatives and professional caregivers.Participation in the intervention will be associated with an increase in empathy and self-efficacy, for both parents/relatives and professional caregivers.

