**Fig. 1 Fig1:**
[figure not shown]
Timeline of the randomized controlled trial. This procedure will be followed separately for the two groups (parents/relatives and professional caregivers)

We report the methods of this study according to the Standard Protocol Items: Recommendations for Interventional Trials (SPIRIT) Checklist (see Additional file 1).

Questionnaires on empathy and self-efficacy will be completed at three time points: at T0, before the intervention starts; at T1, when the intervention is finished; and at T2, when a retention measurement will be taken 30 days after the intervention (Fig. 2).

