### Sample size

The sample size is estimated for linear mixed effects modeling with two conditions, three repeated measures, and clustered data. Based on a pilot study among caregivers in a care center, means and standard deviations can be estimated for empathy, self-efficacy, and knowledge. The desired power is set to a minimum of 0.90 and α = .05. The three care centers are taken into account as clusters with intra cluster correlation of .2. We estimate that around 90 participants are needed to detect a main effect of 0.5 SD on the primary outcome measures. To correct for attrition, we increased the highest number by 10%, bringing the total number of participants to 100 parents/relatives and 100 professional caregivers.

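### As written, the mixed model tests an arm difference averaged over T0, T1 and T2, which shrinks an equal T1/T2 effect by one third and does not measure the hypothesised increase

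*Protocol article*

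**What the plan says.** All from the protocol article:

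- **Primary hypotheses.** These are about change: "Participation in the intervention will be associated with an increase in empathy and self-efficacy", and likewise for knowledge.
- **Study design.** Questionnaires are completed "at T0, before the intervention starts; at T1, when the intervention is finished; and at T2". T2 is described as a retention measurement.
- **Data analysis, aim.** Increases in the three primary outcomes "will be assessed using linear mixed effects modeling. Condition will be entered as a fixed effect".
- **Data analysis, model terms.** "Condition will be entered as a fixed effect and intercepts for participant and care center as random effects".
- **Data analysis, covariates.** "Demographic variables will be included as a covariate in the analysis if significant between-group differences are found at T0". The T0 score of the outcome is not mentioned.
- **Data analysis, analysis set.** Participants with at least two data points are kept.
- **Sample size.** The calculation is for a linear mixed model with two conditions and three repeated measures. "We estimate that around 90 participants are needed to detect a main effect of 0.5 SD on the primary outcome measures". Power is at least 0.90 and α is .05.
- **Knowledge.** "Questions are similar to items in the intervention and differ at each measurement".

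**The concern.** The hypotheses ask whether scores rise more in the intervention arm. A mixed model with condition as its fixed effect and random intercepts for participant and care center estimates something else: the difference in level between the arms, pooled over every measurement in the outcome vector. T0 precedes the intervention, so under randomisation its expected arm difference is zero, and including it pulls the estimate toward zero. The Sample size section is consistent with this reading, because it too speaks of a main effect over three measures.

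Three things are at stake. An effective intervention could be missed. The reported size of effect would be too small. And the single coefficient could not say whether there was an effect at T1 or whether it lasted to T2, although the T2 visit exists to answer that.

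**Working it through.** **Inputs from the article.** Three measures, T0 before the intervention (Study design); effect 0.5 SD, about 90 participants per sample, α = .05, power 0.90, 10% for attrition (Sample size); half of each sample in each condition (Abstract), hence 45 per arm.

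**Assumptions.** The within-person correlation r is not given for this design. I take .62 to .72, the test–retest range that the Empathy section reports for the IRI subscales, as an illustration, and 0.3 to 0.8 as the wider range. Compound symmetry, unit variance, a two-sided test, complete data, and no center or location clustering.

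**The plan's own figure.** The attrition step reproduces: 90/0.9 = 100. The figure of 90 cannot be checked from the stated inputs, because r and the pilot SDs are not given. A 0.5 SD difference in the mean of all three measures at r = 0.3 has variance factor (1 + 2 × 0.3)/3 = 0.533. Then n per arm = 2 × (1.960 + 1.282)² × 0.533/0.25 = 44.8, so 45 per arm and 90 in all. Other combinations also come near 90, so this is compatible with the main-effect reading and does not prove it.

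**What the coefficient estimates.** With effects d1 at T1 and d2 at T2 it is (0 + d1 + d2)/3:

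- d1 = d2 = 0.5: 0.333 SD, a loss of one third that does not depend on r.
- d1 = 0.5, d2 = 0.25: 0.25 SD. The pair d1 = d2 = 0.375 gives the same 0.25, so one coefficient cannot tell a fading effect from a lasting one.
- d1 = 0.5, d2 = 0: 0.167 SD.
- Conversely, a main effect of 0.5 SD over three measures needs 0.5 × 3/2 = 0.75 SD at both T1 and T2.

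Simulated mixed models (60 runs each, n = 90, d1 = d2 = 0.5) gave a mean coefficient of 0.332 at r = 0.3 and 0.326 at r = 0.6. A model with time and a post-baseline condition effect gave 0.505 and 0.477.

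**Power for a true 0.5 SD at T1 and T2.** Power = Φ(δ/SE − 1.96), with SE = √(f × 2/45).

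- Stated model: δ = 0.333, f = (1 + 2r)/3.
- Mean of T1 and T2 adjusted for T0: δ = 0.5, f = (1 + r)/2 − r².

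At r = .62 the stated model has f = 0.747, SE = 0.182 and Φ(1.83 − 1.96) = 0.45. The adjusted analysis has f = 0.810 − 0.384 = 0.426, SE = 0.138 and Φ(3.64 − 1.96) = 0.95.

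| r | Stated model: power (N for 90%) | Adjusted for T0: power (N for 90%) |
|---|---|---|
| 0.3 | 0.58 (202) | 0.89 (96) |
| 0.5 | 0.49 (254) | 0.92 (86) |
| .62 | 0.45 (284) | 0.95 (72) |
| .72 | 0.42 (308) | 0.98 (58) |
| 0.8 | 0.40 (328) | >0.99 (44) |

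The t distribution instead of the normal lowers the stated-model values at .62 and .72 to 0.44 and 0.41; the adjusted ones stay at 0.95 and 0.98. The ratio of sample sizes needed is 0.747 × (9/4)/0.426 = 3.95 at .62 and 0.813 × (9/4)/0.342 = 5.36 at .72.

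**The case against.** The strongest objection is that the article does not say condition is the *only* fixed effect. It is a condensed text, and an analysis plan that is not shown may add time. That stands as a limit on what can be claimed. A reader might infer that the investigators decided to leave time out; the text does not show this. It does name its fixed effect, random effects and covariates, and the sample size rests on the same main effect, so the problem lies in what is stated and not in missing detail.

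Second, the word for increases could mean that change scores are modelled. Condition would then be the difference in change, without dilution. With variance factor 1.5(1 − r), power for the T1/T2 mean minus T0 is 0.87 to 0.95 at r = .62 to .72 (t distribution), and the number needed for 90% power runs from 98 down to 74, which brackets 90. The reading is possible but fits poorly: changes from T0 give two repeated measures, not three, and the sample size speaks of a main effect. Even then, adjusting for T0 does better (0.95 to 0.98) with the same data.

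Third, some stronger inferences should not be drawn:

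- **Chance T0 differences.** Under randomisation they add noise to the coefficient, not systematic bias.
- **Knowledge test.** Different questions at each visit do not bias the arm contrast when data are complete, because a shift in difficulty is common to both arms.
- **Correlation.** The IRI range need not apply to the other outcomes. The Empathy section gives .97 for the EQ, and no value is given for the knowledge test.
- **Clustering.** Power within group homes cannot be computed. The article gives neither the number of homes nor a correlation at that level; its .2 is for care centers.
- **One third.** The factor is exact only for equal T1 and T2 effects and complete data. With 20% missing at T2 the simulated coefficient was 0.354, but 60 runs are too few to separate that from 0.333.

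**Conclusion.** The point holds for the model as written. Followed literally, it estimates a level difference averaged over T0, T1 and T2 and not an increase. A 0.5 SD effect present equally at T1 and T2 is estimated as 0.33 SD, given complete data. This arithmetic needs no assumption about r.

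The loss of power is an illustration. Under the listed assumptions it is about 0.44 to 0.41 against 0.95 to 0.98 at r = .62 to .72, and 0.58 to 0.40 against 0.89 to more than 0.99 over r = 0.3 to 0.8 (normal approximation). These are not the trial's actual power, since r is assumed and clustering is ignored. At every r examined the stated model falls well below the planned 0.90.

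It is not established that the final analysis will use this model, only that the article's text describes it and sizes the trial to match.

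**What to change.** For each primary outcome, in each of the two samples:

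1. Add time as a categorical factor and the condition-by-time interaction.
2. Account for the T0 score. The preferred form keeps T0 in the outcome vector with a common baseline mean for both arms, which retains everyone with any two data points, as the plan intends. The alternative takes T1 and T2 as outcomes with T0 as a covariate. The two are not equivalent when data are missing, because the second drops a participant without T0 unless that value is imputed.
3. Keep the planned random intercepts for participant and care center. Nothing here calls for moving care center to the fixed part.
4. Name the condition contrast at T1 as the effect and the contrast at T2 as retention.
5. Restate the sample-size basis for the named contrast, giving the within-person correlation used and whether the 0.5 SD refers to T1, T2 or their mean.

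The cost is revised analysis text and a redone sample-size calculation. T0 is already collected for every primary outcome, and according to Trial status data collection had not begun at this protocol version.
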